### Participant timeline {13}

A flowchart of this study is shown in Fig. 2, and the participant timeline is presented in Table 1. This study will be conducted in accordance with the Standard Protocol Items: Recommendations for Interventional Trials (SPRIT).

**Fig. 2 Fig2:**
[figure not shown]
The protocol flow chart and timeline of the study

**Table 1 Tab1:**
[figure not shown]
Schedule of enrollment, intervention, and assessment based on SPRIT guidelines

*CAS* Constipation Assessment Scale, *K6* 6-item Kessler Psychological Distress, *QOL* MOS Short-Form 36-Item Health Survey, *POMS*: Profile of Mood States, *GPAQ* global physical activity questionnaire, *HR* heart rate

### Recruitment {15}

Participants will be recruited from among the residents of a local area near Tohoku University, as they are required to visit the university for pre- and post-intervention assessments. Furthermore, those assigned to the intervention group will be required to participate in exercise sessions two to three times per week for 16 weeks. Recruitment will be advertised on a local information paper and distributed free of charge to residents. The contact information of this study, including the barcode URL and email address, will be printed in this paper. Interested residents can reach out using the contact details provided, after which we will respond directly to them. Candidates who meet the inclusion criteria will be contacted to arrange a date for obtaining informed consent.

## Assignment of interventions: allocation

### Sequence generation {16a} and Allocation concealment mechanism {16b}

This study will be conducted as an open-label, randomized controlled trial. Thus, the participants will be randomly assigned to the circuit training or wait-list groups in a 1:1 ratio. Simple randomization will be performed using Research Randomizer (www.randomizer.org), a computer-based random number generator. This web-based service will be used to generate the random sequence for participant allocation to either the circuit training or control group. To ensure allocation concealment, the random allocation sequence will be generated only after each participant is deemed eligible and formally enrolled based on the inclusion and exclusion criteria. Participants will be informed of their group assignments to complete the pre-examination.

### Implementation {16c}

The principal investigator will conduct the abovementioned randomization process to ensure that participants meet all inclusion and exclusion criteria. Once a participant is determined to meet the eligibility criteria and is enrolled, the principal investigator will generate the allocation assignment using the computer-based sequence. Participants will be informed of their group assignment only after the enrollment and baseline assessment procedures are completed. This approach ensures that baseline data collection remains unbiased and unaffected by prior knowledge of group assignment.

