### Who will be blinded {17a}

Owing to the open-label protocol employed in this study, a blinding process will not applied. After announcing group assignments to the participants upon completion of the pre-examination, both the researchers and participants will be aware of the assigned group.

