### Oversight and monitoring

#### Composition of the coordinating center and trial steering committee {5d}

The study protocol and researchers involved are under the supervision of the Ethics Committee of Tohoku University Graduate School of Medicine. The principal investigator will manage the study implementation and collected datasets. The principal investigator’s responsibilities include participant recruitment, ensuring data quality, and participant follow-up. Any modifications to the study protocol or occurrence of adverse events will be promptly reported to the Ethics Committee. The study team convenes weekly meetings to discuss the trial’s progress.

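### The protocol does not settle when the allocation becomes known relative to baseline testing, and its assurance of an unaffected baseline goes further than the procedure it describes

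*Protocol article*

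**What the plan says.** Three adjoining sections of the protocol article deal with allocation and disclosure.

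- **Sequence generation {16a} and Allocation concealment mechanism {16b}.** Simple randomisation in a 1:1 ratio with a public web generator; "the random allocation sequence will be generated only after each participant is deemed eligible and formally enrolled". The section ends: "Participants will be informed of their group assignments to complete the pre-examination".
- **Implementation {16c}.** This section gives the draw and the eligibility check to one person: "The principal investigator will conduct the abovementioned randomization process to ensure that participants meet all inclusion and exclusion criteria". After eligibility and enrolment, "the principal investigator will generate the allocation assignment using the computer-based sequence". On disclosure it then says: "Participants will be informed of their group assignment only after the enrollment and baseline assessment procedures are completed". The section closes with an assurance: "This approach ensures that baseline data collection remains unbiased and unaffected by prior knowledge of group assignment".
- **Who will be blinded {17a}.** "After announcing group assignments to the participants upon completion of the pre-examination, both the researchers and participants will be aware of the assigned group".

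On roles, the section on the coordinating center {5d} states that the principal investigator's "responsibilities include participant recruitment, ensuring data quality, and participant follow-up". The eligibility criteria have serious medical conditions checked by a co-investigator, and the consent section has the researchers taking consent. The article does not say who administers the baseline cognitive tests.

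**The concern.** An assurance that baseline was collected without knowledge of the arm is only as good as the order of three events: the draw, the baseline tests and the disclosure. Here the draw is tied to enrolment, and only disclosure to the participant is tied to completed baseline testing. That protects the participant's ignorance of her arm. It does not protect the ignorance of the person who made the draw. The assurance is worded for baseline data collection as a whole.

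The sentence ending the {16a}/{16b} section adds a second problem. Staff who followed it literally would do the opposite of what {16c} and {17a} require.

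The order matters because the primary cognitive outcome is the change from week 0 to week 16. If knowledge of the arm altered the week 0 score in one group, the alteration would enter the treatment comparison directly.

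**Working it through.** No figure in the plan bears on this point, so the check sets the statements side by side.

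| Question | {16a}/{16b} | {16c} | {17a} |
|---|---|---|---|
| When is the assignment drawn? | After eligibility and formal enrolment | After eligibility and enrolment | Not stated |
| When is the participant told? | Literally, in order to complete the pre-examination | Only after enrolment and baseline assessment | Once the pre-examination is over |
| When do researchers know? | Not stated | The principal investigator knows from the draw | By implication, only after the announcement |

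**Step 1: disclosure to participants.** {16c} and {17a} agree with each other. The {16a}/{16b} sentence, as worded, agrees with neither.

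**Step 2: the two possible orders.**

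- *Draw at enrolment, before baseline testing.* This fits {16c} most naturally: enrolment triggers the draw, and baseline assessment is named separately as what delays disclosure. The principal investigator then knows the arm during baseline collection. The implication of {17a} about researchers fails for that person, and the {16c} assurance is true for participants only.
- *Draw after baseline testing.* The assurance and {17a} then both hold. {16c} can be read this way only loosely, since it nowhere makes the draw itself wait for baseline assessment.

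The text does not say which order applies. Under either, the {16a}/{16b} sentence still needs correcting.

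**Step 3: roles.** The principal investigator makes the draw and confirms eligibility ({16c}) and is responsible for recruitment, data quality and follow-up ({5d}). No separate person who holds or releases the assignment is named.

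**Step 4: how a baseline shift would travel.** Let *b* be a shift in one arm's mean baseline score caused by knowledge of the arm, with week 16 unaffected.

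- Difference in change: (post) − (pre + *b*), so the comparison moves by −*b*, the whole shift.
- Model with baseline as a covariate and slope β: the comparison moves by −β*b*, a part of the shift.

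For cognition, the statistical methods list age and sex as adjustments. Baseline values are named as covariates for the gut and protein outcomes, and a later paragraph refers to a random-intercept mixed model as the handling of baseline. Neither route brings the effect to zero unless *b* or β is zero. The document gives no value for *b*, so the calculation ends here.

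**The case against.** The strongest reply is that nothing in the article states that the draw comes before baseline testing, and that {17a} points the other way by having researchers become aware after the pre-examination. That stands: the early draw is an inference from how {16c} is built. It is still the natural reading, and the uncertainty is itself the defect, because the assurance depends on the order.

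Four stronger readings are tempting, and the document does not support them.

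- *Participants are tested knowing their arm.* This rests on the one sentence in {16a}/{16b}, which is most likely a slip for being told upon completing the examination. Two explicit statements contradict it. It calls for correction and does not prove early disclosure. Without early disclosure, a participant's expectation of benefit cannot affect her effort at baseline.
- *The tester knows the arm.* The tester is not identified. The flanker, n-back and source memory tasks run on a computer, which leaves little room for influence; the Stroop task is on paper.
- *Enrolment can be selective.* With simple randomisation drawn only after enrolment, no assignment exists to be foreseen when a woman is accepted. The procedure is sound in this respect, and a sequence generated wholly in advance would be a preference rather than an improvement the trial needs.
- *One person does everything.* {5d} lists responsibilities, which need not mean performing each task, and a co-investigator and other researchers take part in screening and consent. The overlap of draw, eligibility check and oversight is real but narrower than it may look.

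A repeated draw is conceivable, but the article's silence on logging does not show that none exists. The full protocol may cover it. The participant flow chart and schedule table could not be read in the text at hand and may also show the intended order.

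**Conclusion.** The point holds as an inconsistency and an over-wide assurance, and it is worth correcting. The three sections do not agree on when the group becomes known. On the natural reading of {16c}, the principal investigator can know the arm while baseline is collected, which the closing assurance of that section and the implication of {17a} both deny.

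Its size cannot be stated. Any number for the resulting bias would only return an assumed baseline shift, so none is offered. A reader might infer that the baseline scores are biased. The document does not show this: it would take a draw made before testing, a tester who knew its result, and an influence on the scores, and the document establishes none of the three. What is shown is that the procedure described leaves open a route to bias in a change-from-baseline outcome, and that the route can be closed at almost no cost.

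The conclusion assumes that enrolment in {16c} is a step before baseline assessment, as the section's own separate naming of the two suggests. If the draw was in fact always made after baseline, only the wording needs repair.

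**What to change.** 1. Reword the last sentence of {16a}/{16b} so that participants learn their assignment only after completing the pre-examination, in line with {16c} and {17a}.
2. State in {16c} that each assignment is generated and released only after that woman's baseline assessments are complete, with a time-stamped record of the draw, preferably made by an existing team member who takes no part in recruitment or testing. Drawing one participant at a time can stay as it is.
3. For women already enrolled, report the dates of draw and of baseline testing. Where the draw came first, limit the {16c} assurance to participants' knowledge of their group.

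The cost is a wording change, one step moved later and handed to someone already on the team, and a short table of dates. According to Trial status, recruitment began in June 2024 and was expected to finish by February 2025. If it has closed, item 2 no longer applies, and items 1 and 3 remain possible in an amendment or in the results report.

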### Who will be blinded {17a}

Owing to the open-label protocol employed in this study, a blinding process will not applied. After announcing group assignments to the participants upon completion of the pre-examination, both the researchers and participants will be aware of the assigned group.

### Procedure for unblinding if needed {17b}

Not applicable as no blinding will be used in this trial.

### Data collection and management

#### Plans for assessment and collection of outcomes {18a}

In this paper, we list each scale (e.g., Short Grit Scale, Brief Resilience Scale, Self-Theories of Intelligence Scale) along with its psychometric properties, scoring procedures, and references for validity and reliability. Second, we clarify the measurement timeline, indicating that all scales will be administered at baseline and at 16 weeks. Finally, we will ensure consistency between Sect. 18a and the Outcomes section by explicitly mapping each scale to its corresponding study outcome or exploratory variable (e.g., resilience as a psychological characteristic, perceived stress as a mental health indicator).

### Cognitive task

In this study, cognitive function will be assessed using both the pencil-and-paper and computer-based versions. The computer-based version will be conducted using PsychoPy, which uses the Python programming language.

We will use a paper-and-pencil version of the Stroop task, as described in a previous study [48], to assess inhibitory control. This task will include four conditions: two neutral, one Stroop, and one reversed Stroop. The Stroop paradigm comprises four conditions. In Neutral Condition 1, participants see color words (e.g., “RED”) printed in black ink, which serves as a baseline measure of word processing. In the Reverse-Stroop Condition, participants see incongruent color-word combinations (e.g., the word “RED” printed in blue ink) and must select the color meaning of the word (“RED”) rather than its ink color. Neutral Condition 2 presents colored patches (e.g., a red box) where participants mark the corresponding color name, serving as a baseline for color processing. Finally, in the Stroop Condition, participants see incongruent color-word combinations (e.g., the word “RED” printed in blue ink) and must indicate the ink color (“blue”) rather than the word’s meaning. In all conditions, the participants will be instructed to respond as quickly and accurately as possible within 60 s. This task measures the number of correct items.

The Flanker task, which incorporates both congruent and incongruent conditions, serves as a method for evaluating inhibitory control through a computer-based implementation (Fig. 3). Participants will be instructed to respond as quickly and accurately as possible by pressing “c” or “m” keys, corresponding to the direction of the target arrow. If the target arrow points to the left, participants should press the “c” key; if it points to the right, they should press the “m” key. This task contains 100 trials including congruent (i.e., > > > > > or < < < < <) and incongruent (i.e., < < > < < or > > < > >) arrows. Each array will be displayed for 300 ms, followed by a fixed inter-stimulus interval of 1400 ms. This task will measure the number of correct items and the reaction time (RT).

**Fig. 3 Fig3:**
[figure not shown]
Examples of stimuli and correct judgments in Flanker task

The N-back task is commonly used to evaluate the working memory. This study employs computer-based 1-back (Fig. 4) and 2-back (Fig. 5) tasks, displaying numbers from one to nine on the display. Participants will need to respond with “c” and “m” keys according to a non-target and target and stimuli, respectively. In the 1-back task, participants will be instructed to respond with the “m” key as a target when a number appears as the same number presented one trial ago, and otherwise to respond with the “c” key as a non-target. In the 2-back task, participants will be instructed to respond with the “m” key as a target when a number appears as the same number presented two trials ago, and otherwise to respond with the “c” key as a non-target. The two tasks (i.e., one-back and two-back) consist of 90 trials with a 30% probability of the target appearing in each trial for all tasks, presenting a fixation for 2000 ms, followed by presenting a stimulus of number for 500 ms. Participants will be instructed to respond as quickly and accurately as possible. This task measures the number of correct items and RT.

**Fig. 4 Fig4:**
[figure not shown]
Examples of stimuli and correct judgments in 1-back task

**Fig. 5 Fig5:**
[figure not shown]
Examples of stimuli and correct judgments in 2-back task

The source memory task, which includes the encoding and retrieval phases, will be administered using a computer-based implementation (Fig. 6). The task paradigm is developed according to a procedure described in a previous study [49]. During the encoding phase, participants will be asked to memorize the presented white and black picture. They will also be asked to judge whether the picture depicts a natural (e.g., fruit and animal) or an artificial object (e.g., car and house). The pictures appear randomly on a display divided into four equal sections, both vertically and horizontally, with a grit layout line. The stimuli of the picture will be presented for 1500 ms, followed by an equal section interval of 2500 ms. The participants will be instructed to respond as accurately and quickly as possible. In the retrieval phase, the participants will be asked to press two keys (c: new, m: old) corresponding to whether the presented picture is old or new. When participants judge the picture to be old, the grid layout line divided into four equal sections will appear. Participants will need to press four keys (i.e., v, f, n, j) corresponding to where the old picture was presented. In total, 120 black-and-white outline picture are selected from a previous study [50]. For the encoding and retrieval phases, 108 pictures are selected, including three sets (i.e., 36 pictures per set) of equationally distributed natural and artificial objects. During the encoding phase, 72 images will be displayed. Thirty-six additional images will be presented during the retrieval phase. The remaining 12 images will be used in the practical phase of the task.

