By combining randomized assignment with multi-level statistical methods, we can:Measure how the exercise intervention alters gut microbiota/metabolite, inflammatory/anti-inflammatory cytokines, and aging-related proteins;Identify the biomarkers or pathways most strongly associated with improvements in cognitive outcomes; andElucidate possible mediating mechanisms (e.g., exercise → gut microbiota → SCFA → cognition, exercise → SIRT/mTOR → cognition).

The primary outcome of this study is cognitive function, which will be assessed by comparing changes from baseline to 16 weeks after the intervention. We will evaluate four key cognitive domains using standardized tasks. Executive function and attention will be measured using a paper-and-pencil version of the Stroop task, analyzing changes in both reaction time (milliseconds) and error rates. Selective attention and response inhibition will be assessed using a computerized Flanker task, measuring changes in accuracy (percentage of correct responses) and reaction time. Working memory capacity and updating will be evaluated using an n-back task (with *n* = 1 and *n* = 2 conditions), examining changes in accuracy and reaction time. Finally, hippocampal-dependent memory function will be assessed through a source memory task, measuring changes in accuracy of responses. All these measurements will compare performance between baseline (week 0) and the end of the intervention period (week 16). In terms of compliance criteria and statistical analysis of non-compliance, participants must attend at least two sessions per week. Based on previous research [44] demonstrating cognitive improvements with ≥ 70% attendance, we will establish a 70% compliance threshold. For the main analysis, we will include participants who completed both pre- and post-intervention assessments, with missing data handled using the multiple imputation method and a machine learning approach, such as random forests. Furthermore, if notable variation in attendance occurs, we will conduct stratified analyses using the 70% threshold to explore potential dose–response relationships.

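### As described, one sitting of the source-memory task uses every test picture, so all 36 'new' pictures at week 16 were already shown at baseline

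*Protocol article*

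**What the plan says.** The Cognitive task section gives a full inventory of the stimuli. The pool is fixed first: "In total, 120 black-and-white outline picture are selected from a previous study". The test material is then set out: "For the encoding and retrieval phases, 108 pictures are selected, including three sets (i.e., 36 pictures per set". Its use within a sitting follows: "During the encoding phase, 72 images will be displayed" and "Thirty-six additional images will be presented during the retrieval phase". The rest is assigned to practice: "The remaining 12 images will be used in the practical phase of the task".

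At retrieval each picture is first judged old or new. Location is asked only after an old response: "When participants judge the picture to be old, the grid layout line divided into four equal sections will appear".

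Outcomes {12} makes the task part of the primary outcome: "hippocampal-dependent memory function will be assessed through a source memory task, measuring changes in accuracy of responses". It also sets two administrations: "All these measurements will compare performance between baseline (week 0) and the end of the intervention period (week 16". The same section names no other task for memory, and Objectives {7} hypothesises that training improves memory.

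The article mentions no second picture list, parallel form or counterbalancing of sets between visits.

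**The concern.** In a source-memory task the pictures themselves carry information from one visit to the next. The flanker arrows and n-back digits do not, so repeating those is a smaller matter. Here the correct week-16 answer to a foil is new, yet the woman was shown that picture 16 weeks earlier. Any memory of it favours the answer scored as wrong. A studied picture may also bring back a location from baseline. If locations are redrawn, that memory can conflict with the current one. If they are kept, the location is being learned a second time.

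The baseline score is free of all this. The change from week 0 to week 16 therefore compares two somewhat different measurements, and no other task can carry the memory hypothesis.

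**Working it through.** **Inputs** (Cognitive task, {18a}): pool 120; test pictures 108 in three sets of 36; 72 encoded; 36 added at retrieval; 12 for practice. From Outcomes {12}: two administrations.

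**1. The article's own total.** 3 × 36 = 108. One sitting uses 72 + 36 = 108. With practice, 108 + 12 = 120. This reproduces the stated total exactly.

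**2. Pictures left for week 16.** 120 − (72 + 36 + 12) = 0. So 36 of 36 week-16 foils (100%) and 72 of 72 studied pictures were shown at baseline. Rotating the three sets changes only whether a week-16 foil was a studied picture or a foil at baseline. It cannot make any foil unseen.

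**3. Conflicting locations, if quadrants are redrawn at random.** The chance that a redrawn quadrant differs from the earlier one is 3/4.
- Same 72 studied again: 0.75 × 72 = 54 of 72 (75%).
- The 36 baseline foils rotated into the studied set: only 36 of the 72 have an earlier location, so 0.75 × 36 = 27 of 72 (37.5%).
- Quadrants not redrawn and the same 72 studied: no conflict, but the locations are relearned.

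**4. Direction of the effect on old/new accuracy.** Suppose leftover familiarity raises the chance of an old response by the same amount d on every picture. It adds 72d correct answers among studied pictures and removes 36d among foils. The net change in proportion correct is (72d − 36d)/108 = d/3, an increase. Foil accuracy alone falls by d. The sign depends on which score is used, and Outcomes {12} does not say how old/new and location responses are combined.

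**5. Pictures needed to avoid overlap.** Two disjoint sittings of the stated length need 2 × 108 = 216 test pictures: 228 in total with shared practice pictures, 240 with separate ones. Fresh foils alone need 108 + 36 = 144 test pictures, or 156 with practice. Splitting the existing 108 gives 54 per visit (36 studied + 18 new).

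**6. Cost of splitting.** Assume 70% source accuracy (not in the document) and that every studied picture is scored for location. The per-woman standard error is √(0.7 × 0.3/72) = 0.054 with 72 pictures and √(0.7 × 0.3/36) = 0.076 with 36, that is, 5.4 and 7.6 percentage points. Because location is asked only after an old response, the denominators would be smaller unless misses count as source errors.

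**The case against.** The strongest reply has three parts.

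First, the article nowhere says which pictures are used at week 16, and visit-specific lists could sit in the full protocol. It is true that the repetition is inferred from the counts. But the article does more than stay silent. It states a total and assigns every picture to a use, so a second list would have to lie outside that stated total.

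Second, both arms see the same pictures, and under Implementation {16c} women learn their group only after baseline. Repetition alone therefore does not bias the randomised comparison, and an average practice effect cancels. This stands. A difference between arms would need appreciable retention over 16 weeks and an effect of training on the carry-over. The document shows neither, and each studied picture is displayed for only 1500 ms.

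Third, the direction is open. A reader might infer that better memory lowers the week-16 score, so that a true benefit is pulled toward or past zero. The document does not support this. It follows for foils taken alone, or for redrawn locations. Familiarity can also raise hits on 72 pictures while costing on 36, unchanged locations would help, and better recollection could help a woman tell the two lists apart. Nor may one say in general that most studied pictures carry a conflicting location: under set rotation the expected share is 37.5%. Finally, the counts show prior exposure and not how much is remembered.

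**Conclusion.** The point holds as a weakness of measurement. As described, the task leaves no unseen picture for week 16, and all 36 foils had been shown at baseline. The week-16 old/new and location scores mix memory for the current list with carry-over, which makes the change score harder to interpret on the only memory measure in the primary outcome.

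The overlap of 100% rests on reading 120 as the whole pool and on the stated two administrations. The 75% and 37.5% figures assume that quadrants are redrawn at random. No bias in a given direction is shown, and its size cannot be computed, because the document gives no retention figure and no combined scoring rule. The comparison remains fair under no effect of training. The change is worth making because it is cheap and no other task measures memory.

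**What to change.** - **Week 16, both arms:** use a second list of 72 + 36 pictures that does not overlap the first, drawn if possible from the same published set and matched on natural and artificial objects. State in the protocol which pictures are used at each visit and how locations are set.
- **Women not yet tested at baseline:** assign list order at random, independently of treatment allocation, so that handing out a list at baseline does not require knowing the arm.
- **Women tested at baseline but not yet retested:** give the second list at week 16 in both arms.
- **If the source set is too small** (its size is not given): split the 108 into two forms of 36 studied + 18 new. This serves only women not yet tested at baseline, since the others have already seen all 108.
- **Women already retested on the same pictures:** record the list used, report foil false alarms and source accuracy separately, run a sensitivity analysis by list version, and qualify the memory conclusion. Recruitment began in June 2024 and was expected to end by February 2025 (Trial status), so this group may be large.

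The cost is a second stimulus list in the existing PsychoPy task and a short amendment. The downside is a possible difference in list difficulty, which is shared by both arms. If the pool must be split, the per-woman error rises from about 5.4 to 7.6 percentage points under the assumptions above. If a second list already exists, one sentence saying so settles the point.
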